**Methods:**

This study is an ongoing single-center prospective observational study, with a plan to recruit at least 556 hospitalized older adults living with HIV or AIDS (n=445 for development and n=111 for validation). According to the theory of unpleasant symptoms, candidate predictors are categorized into physiological factors (including sociodemographic factors, disease-related influencing factors, sleep, nutrition, and neurocognitive function), psychological factors (including anxiety and depression status), and environmental factors (including social support status). Potential predictors are screened using univariate analysis and least absolute shrinkage and selection operator regression to identify variables for final model inclusion. Model construction and validation employ 3 standard machine learning algorithms: logistic regression, random forest, and support vector machine. Model performance will be evaluated by reporting accuracy, precision, sensitivity, specificity, and the area under the curve.

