### Prediction Variables

#### Determination of Candidate Variables

The selection of predictive variables for this prediction model is based on a review of literature and consensus opinions by an expert group, taking into account its practicality in clinical settings. Possible clinically relevant variables will be selected as candidate predictors of frailty and evaluated after the patient’s admission examination is completed. Through 3 group discussions and 1 online expert consultation meeting, a total of 31 candidate predictor variables were identified and classified into physiological, psychological, and environmental factors based on TOUS. The variables to be explored are detailed in the following subsections.

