### Model Development and Validation

The sample size of this study is relatively small. This study uses logistic regression (LR) as the benchmark for performance comparison. LR has certain advantages in handling limited sample sizes and can demonstrate feature coefficients and significance levels. Although random forest (RF) has the risk of overfitting in small sample situations, it has certain advantages in handling complex nonlinear relationships. We will minimize the risk by adjusting decision tree parameters and cross-validation. Support vector machine (SVM) is particularly suitable for handling situations with high feature dimensions but relatively small sample sizes, and its regularization properties help control the risk of overfitting. As one of the tree ensemble algorithms, XGBoost also has the risk of overfitting and relatively complex parameter tuning. Neural networks have high requirements for sample size and poor clinical interpretability for small sample studies. We hope to ensure the robustness of the model to a large extent in this small sample study. For future larger-scale research, more complex machine learning methods will be used.

Randomly split the training set and validation set in a 7:3 ratio, and use the following machine learning algorithms for modeling: LR model, RF, and SVM. Univariate analysis combined with least absolute shrinkage and selection operator regression will be used to screen predictive factors. To address nonlinearity, we will analyze the relationships between relevant factors and HIV frailty risk using restricted cubic splines and incorporate them as spline terms in the model. Restricted cubic splines can also indirectly capture potential interactions between features. Interactions and complex nonlinear decision boundaries will be handled by selecting nonlinear kernel functions in SVM. The primary model performance evaluation metric is accuracy, which represents the proportion of correctly predicted samples in classification tasks. This will be considered alongside precision, recall, *F*_1_-score, and area under the receiver operating characteristic curve for comprehensive assessment. Through integrated comparison, the algorithm achieving optimal balance across these metrics will be selected as the final model for predicting frailty status in people with HIV.

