To prevent overfitting, the nonlinear modeling effects of all models will be validated via cross-validation. A 3×10-fold cross-validation scheme will be adopted, with each split performed independently, yielding 30 model performance estimates (eg, area under the curve [AUC], *F*_1_-score). Overfitting will be monitored by ensuring that the performance difference between the training set and the cross-validation set remains below a threshold (AUC difference <0.05). During cross-validation, hyperparameters (including max_depth for RF, and C and γ for SVM) will be jointly optimized to select the parameter combination that achieves the best trade-off between fitting efficacy and generalization ability, thereby further reducing overfitting risk. The final model selected through cross-validation will then be evaluated on an independent test set for ultimate performance assessment. For internal validation, we performed bootstrap resampling (n=1000 iterations) to generate training sets matching the original cohort size. Retraining prediction models with these training sets and evaluating performance using the above indicators, we will repeat this process to obtain internal validation performance. External validation will be implemented in prospective observational studies, using external period validation to analyze samples from September 1, 2025 to December 31, 2025. In future research, we plan to collaborate with other institutions to continue external validation. The sample size required for external validation in this study is 1/4 of the modeling sample size, and the minimum sample size for external validation is calculated to be 139 cases (Figure 1).

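### After univariate and LASSO screening of 31 candidates the logistic model has no stated shrinkage, so its predicted frailty risks are likely to be too extreme (calibration slope roughly 0.6 to 0.87, depending on assumptions)

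*Protocol article*

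**What the plan says.** Under Determination of Candidate Variables, "a total of 31 candidate predictor variables were identified". The abstract's Methods paragraph describes univariate analysis and "least absolute shrinkage and selection operator regression to identify variables for final model inclusion". Model Development and Validation repeats the role: "Univariate analysis combined with least absolute shrinkage and selection operator regression will be used to screen predictive factors". The same section then lists the models to be built: "use the following machine learning algorithms for modeling: LR model, RF, and SVM".

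On the logistic model the article says two things: "This study uses logistic regression (LR) as the benchmark for performance comparison", and "LR has certain advantages in handling limited sample sizes and can demonstrate feature coefficients and significance levels". Regularisation is mentioned as a property of the support vector machine (SVM). Tuning is described as follows: "hyperparameters (including max_depth for RF, and C and γ for SVM) will be jointly optimized". No penalty or shrinkage factor is named for LR.

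Performance is judged on accuracy (primary), precision, recall, F1 and AUC; the abstract adds specificity. Overfitting is monitored by an AUC difference below 0.05. Internal validation uses 1000 bootstrap resamples with retraining, judged on the same indicators.

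**The concern.** A LASSO fit does two things at once: it drops variables, and it pulls the remaining coefficients towards zero. If only the list of survivors is kept and LR is refitted to them by maximum likelihood on the same patients, the shrinkage is lost. The coefficients then carry the optimism of having been chosen because they looked large. A univariate screen on the same data adds to this.

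The result is a calibration slope below 1 in new patients. With a slope of 0.75, a difference of one unit in predicted log-odds corresponds to only 0.75 in true log-odds. High predicted risks are too high and low ones too low.

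None of the named safeguards would show this. AUC depends only on ranking, which a rescaling of the linear predictor does not change. An AUC gap, cross-validated AUC or bootstrapped accuracy can all look sound while the risks themselves are wrong.

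**Working it through.** **1. Reproducing the plan's figure.** Inputs from Sample Size: R² = 0.1483, P = 10 parameters, prevalence 0.593. The quoted call states no shrinkage target, so the package default S = 0.9 is assumed.

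n = P / [(S − 1) ln(1 − R²/S)] = 10 / [(−0.1) × ln(1 − 0.1483/0.9)] = 555.4, rounded up to 556.

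The other two criteria give 244 and 371, so this one drives the sample size. Events: 556 × 0.593 = 329.7, or 33.0 per parameter. The stated 556, 330 and 33 all reproduce. The study is thus sized for a shrinkage of 0.9 with 10 parameters.

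**2. The same formula at the sizes and candidate count in the article.** The 7:3 split gives 0.7 × 556 = 389 for training; Patient Recruitment gives 445 for development. Solving for S, with each candidate counted as one parameter:

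| Parameters | n = 556 | n = 445 | n = 389 |
|---|---|---|---|
| 10 | 0.900 | 0.878 | 0.864 |
| 31 | 0.748 | 0.705 | 0.677 |

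The smaller training set alone misses 0.9, even with 10 prespecified predictors. Searching 31 candidates widens the gap considerably.

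**3. Simulating the sequence.** Fixed from the article: R² 0.1483, prevalence 0.593, 31 candidates, univariate P < .05, then LASSO. Assumed: normal predictors, the correlation and effect patterns below, and a cross-validated penalty. Slopes are means over repeated datasets, measured in 20,000 new patients.

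| Assumed pattern | n | LR refitted | LASSO coefficients kept |
|---|---|---|---|
| 5 or 10 true effects, correlation 0.1–0.3 | 389 | 0.74–0.82 | 0.91–1.11 (both sizes) |
| same | 556 | 0.81–0.87 | as above |
| 10 true, equal correlation 0.1 | 389 / 556 | 0.79 / 0.82 | 0.97 / 1.00 |
| 5 true, equal correlation 0.3 | 389 / 556 | 0.83 / 0.85 | 1.15 / 1.14 |
| 8 equal, or 5 stronger plus many small; correlation 0.2 decaying with distance | 389 | 0.75–0.77 | 0.80–0.83 |
| same | 445 | 0.79–0.81 | 0.84–0.86 |
| all effects weak, same correlation | 389 | 0.58 | 0.64 |

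A further run gave refit slopes of 0.75 (n = 389), 0.79–0.83 (n = 445) and 0.79 (n = 556). A repeat of the first pattern reached 0.88 at n = 556. Rounded, the range is about 0.6 to 0.87.

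**4. Separating the causes.** Without the univariate screen, on the decaying-correlation patterns at n = 389, the refit gives 0.62–0.63 and the kept LASSO coefficients 1.03–1.06. There the lost shrinkage explains the gap. With the screen, keeping the LASSO coefficients gains only about 0.05 on those patterns. With equal correlation it gains more: 0.97 − 0.79 = 0.18 to 1.15 − 0.83 = 0.32. The share due to each cause therefore depends on how the predictors correlate.

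**5. What is not affected.** With 10 true effects at n = 389, AUC is 0.702 refitted and 0.700 with LASSO coefficients kept; differences are about 0.002 or less throughout.

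**6. The remedy.** A bootstrap shrinkage factor that repeats the screening in each resample brought the slope to 0.97–1.05 with accuracy unchanged. In one further setting (n = 389, at most 10 variables retained) it moved the slope from 0.736 to 0.930.

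**The case against.** The strongest reply is that the article nowhere says LR is refitted without a penalty. The remark that LR "can demonstrate feature coefficients and significance levels" is a general reason for using it as a benchmark, the tuning list is introduced as a partial one, and a condensed article may leave the estimator to the full plan. This stands to the extent that the unpenalised refit must be called an inference. It does not remove the point: the article itself fixes a select-then-fit sequence, credits regularisation to SVM and tuning to random forest (RF) and SVM, and values LR for output that belongs to an ordinary fit.

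Second, selecting with LASSO and refitting is common practice, and the objective of identifying associated factors is a reason to report ordinary coefficients. That is fair. Those coefficients can still be reported beside a shrunken prediction equation.

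Third, the declared task is classification, and accuracy and AUC barely move. This is correct and limits the consequence to the predicted risks.

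Fourth, a reader might infer that the discarded LASSO shrinkage is the whole cause and that keeping the LASSO coefficients is the cure. The checks do not support this. The screen, the 31 candidates and the split contribute too. The gain can be as small as 0.05, and the outcome depends on which penalty is taken: the one-standard-error penalty gave kept-coefficient slopes of 1.6–1.9 in reruns, further from 1 than the refit (0.74–0.90). Nor would a linear screening LASSO supply the spline terms that the article plans to include.

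**Conclusion.** The point holds in a conditional form. If LR is fitted by maximum likelihood after the screening, as the text most naturally reads, its risks will probably be too extreme, with a mean calibration slope of roughly 0.6 to 0.87 against the 0.9 that underlies the 556.

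That range is not a figure from the article. It rests on the plan's R² and prevalence, on a development size between 389 and 556, and on assumed effect and correlation patterns. A stronger signal softens it only in part: at R² 0.30 and n = 389 the refit gave 0.73–0.83.

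A reader might also infer that the logistic equation will be the tool used at the bedside. The article does not say so: LR is the benchmark, and whichever of LR, RF and SVM best balances the metrics becomes the final model. The point concerns the LR model only and is a cheap improvement, not a threat to the study's discrimination results.

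**What to change.** In Model Development and Validation, state how the LR coefficients are shrunk, using the 1000 bootstrap resamples already planned:

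1. Draw each resample from the data in which the LR model is fitted, and repeat the univariate screen, the LASSO selection and the LR fit in full.
2. Apply each resulting model to the original data and record its calibration slope.
3. Take the mean of these slopes as a uniform shrinkage factor.
4. Multiply all LR coefficients, spline terms included, by this factor and re-estimate the intercept.
5. Publish the shrunken equation together with its calibration slope.

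This corrects for the screen and the selection together, whatever their shares. The cost is a sentence or two and a few lines of code; the article states that no data analysis has yet been done. The downside is a little more analysis and published coefficients somewhat smaller than those of the ordinary fit, which can still be reported for the objective on associated factors.

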**Conclusions:**

The findings of this study are expected to provide clinicians in the department of infectious diseases with a convenient tool for frailty risk prediction, thereby enabling early intervention and ultimately improving the long-term health status and quality of life of people living with HIV.

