Currently, unidimensional frailty assessment remains predominant in research involving people living with HIV or AIDS, while research on multidimensional frailty status is still insufficient, and the factors leading to multidimensional frailty in hospitalized older adults living with HIV or AIDS are not yet clear. Therefore, we will explore multidimensional frailty as the main outcome. The theory of unpleasant symptoms (TOUS), as a mid-level theory, is commonly used to establish methodological methods and analyze results, or as a theoretical framework for analyzing influencing factors [13,14]. The theory suggests that factors that affect symptoms can be divided into 3 parts: physiological, psychological, and environmental. The three interact and influence each other, jointly affecting disease symptoms and influencing the outcome of symptoms. Guided by TOUS, we categorized potential frailty factors in hospitalized older adults living with HIV or AIDS into physiological, psychological, and environmental domains based on literature review and clinical practice. Ultimately, all included potential influencing factors were identified and finalized through online expert consultation.

Early-stage frailty in older adults living with HIV or AIDS is often relatively insidious. However, to our knowledge, there is relatively little research and development in China on frailty prediction tools for hospitalized population. To address these gaps, we aim to develop and validate a prediction model using 3 machine learning algorithms. By comparing their performance, we seek to enhance risk prediction accuracy, ultimately improving patient prognosis and health outcomes.

This prospective observational study aims to (1) determine the prevalence of multidimensional frailty among hospitalized people living with HIV or AIDS aged ≥50 years, (2) identify factors associated with frailty guided by the TOUS, and (3) develop and validate risk prediction models.

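### Accuracy is the primary metric and no calibration measure is listed for a risk prediction tool, so over-extreme predicted risks with unchanged ranking would go undetected

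*Protocol article*

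**What the plan says.** Under Model Development and Validation, the protocol article names a primary metric: "The primary model performance evaluation metric is accuracy, which represents the proportion of correctly predicted samples in classification tasks". Companion metrics follow: "This will be considered alongside precision, recall", then F1-score and AUC. The choice between logistic regression, random forest and support vector machine is left to a balance: "the algorithm achieving optimal balance across these metrics will be selected as the final model". No weights or order of priority are attached, and no probability cut for accuracy is stated.

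The Abstract (Methods) gives a second list: "Model performance will be evaluated by reporting accuracy, precision, sensitivity, specificity, and the area under the curve".

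The same section on model development sets the checks against overfitting. These are repeated 10-fold cross-validation with the "performance difference between the training set and the cross-validation set remains below a threshold (AUC difference <0.05"), hyperparameter tuning, an independent test set, a bootstrap ("For internal validation, we performed bootstrap resampling (n=1000 iterations")) scored on the metrics already named, and a temporal validation sample.

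The third aim in the Introduction is to "develop and validate risk prediction models", and the Abstract's conclusion promises clinicians "a convenient tool for frailty risk prediction". Neither metric list, nor any other part of the article, mentions a calibration slope, intercept, calibration plot, Brier score or log-loss.

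**The concern.** A tool that outputs risk has to meet two requirements: it must rank patients correctly, and a predicted 80% must correspond to about 80% observed. AUC addresses the first. Accuracy, precision, recall, F1 and specificity address classification at a cut. Nothing listed addresses the second. A model whose risks are too extreme can match a well-calibrated one on every listed metric.

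Accuracy is also a poor lead metric here because it depends on prevalence and on the chosen cut. At the prevalence the article assumes, it starts from a high no-skill value. With no weights on the balance of metrics, the preferred algorithm can be settled after the results are seen.

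The sample size makes the gap more visible. The stated N follows from a criterion that limits expected shrinkage, which is a calibration-slope target, yet the analysis lists no measure of that slope.

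**Working it through.** **Inputs.** From Sample Size: prevalence p = 0.593, Cox-Snell R² = 0.1483, 10 parameters, N = 556. From Determination of Candidate Variables: 31 candidates. From Model Development and Validation: 7:3 split, so 0.7 × 556 ≈ 389 for training. Assumed, because the article does not state them: shrinkage target S = 0.9 (taken as the package default), a classification cut of 0.5, and a normally distributed linear predictor.

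**1. The article's own sample size.**
- Shrinkage criterion: n = P / [(S − 1) ln(1 − R²/S)] = 10 / [(−0.1) × ln(1 − 0.1483/0.9)] = 10 / (0.1 × 0.18006) = 555.4, rounded up to 556. This reproduces the stated figure.
- Events: 556 × 0.593 = 329.7, or 33 per predictor, as stated.
- The other two criteria need 244 (optimism in R² of at most 0.05) and 371 (overall risk within 0.05).

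So the shrinkage criterion sets N.

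**2. No-skill floor.** Calling every patient frail at p = 0.593 gives accuracy 0.593, precision 0.593, recall 1, F1 = 2 × 0.593 / 1.593 = 0.744, specificity 0 and AUC 0.50. The majority-class accuracy is max(p, 1 − p): 50% at a prevalence of 50%, and 70% at 70%.

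**3. What the listed metrics can see.** A linear predictor that matches p = 0.593 and R² = 0.1483 has mean 0.444 and SD 0.923. The log-odds are multiplied by k and patients classified at 0.5.

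| | k = 1 | k = 2 | k = 3 |
|---|---|---|---|
| Accuracy | 0.679 | 0.679 | 0.679 |
| Precision | 0.699 | 0.699 | 0.699 |
| Recall | 0.807 | 0.807 | 0.807 |
| F1 | 0.749 | 0.749 | 0.749 |
| Specificity | 0.493 | 0.493 | 0.493 |
| AUC | 0.726 | 0.726 | 0.726 |
| Calibration slope (1/k) | 1.00 | 0.50 | 0.33 |
| Brier score | 0.205 | 0.218 | 0.235 |

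For scale, predicting 0.593 for everyone has a Brier score of 0.593 × 0.407 = 0.241. At k = 2 the share of the cohort with a predicted risk above 90% rises from 3% to 24%, with mean predicted risk 95% against 83% observed.

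**4. Dependence on the cut.** A probability of 0.5 is log-odds 0, which multiplication does not move. At other cuts the threshold metrics do shift between k = 1 and k = 2. At 0.593, recall goes from 0.66 to 0.74 and specificity from 0.67 to 0.58. At 0.7, accuracy goes from 0.606 to 0.660, so the miscalibrated model scores higher. AUC never changes.

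**5. What the planned overfitting check can see.** Unpenalised logistic regression was simulated on 389 patients, with equally weighted normal predictors and no LASSO step. Fresh data stand in for the cross-validation folds.

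| Predictors | Training AUC | Fresh-data AUC | Gap | Against 0.05 limit | Slope |
|---|---|---|---|---|---|
| 31 | 0.777 | 0.683 | 0.094 | fails | 0.58 |
| 10 | 0.742 | 0.711 | 0.031 | passes | 0.85 |

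**The case against.** The strongest reply is that the article takes overfitting seriously. It plans cross-validation with an AUC-gap limit, tuning, a bootstrap, a test set and temporal validation. A reader might infer from step 3 that a badly overfitted model would score as well as a sound one. The article does not support that. Multiplying the log-odds is pure miscalibration; real overfitting also disturbs the ranking and lowers held-out performance, and in the 31-predictor simulation the article's own limit is breached. What remains is the milder case: with 10 predictors the check passes at a slope of 0.85.

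A reader might also infer that a rule calling everyone frail could win. It could not do so unseen, because accuracy is not used alone: AUC of 0.50 and specificity of 0 would expose it. The 59.3% itself comes from a different frailty scale from the Tilburg indicator used for the outcome here, so the floor is an assumption.

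Two further points stand. The exact invariance of the threshold metrics needs the 0.5 cut, which the article does not state. And nothing in the article says that individual probabilities will be handed to patients; some of its wording describes classifying frailty status. It is likewise not shown that the algorithm would be chosen on noise.

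Finally, this is a condensed article, and a fuller plan might add calibration. That explains a missing plot. It does not explain an explicit choice of primary metric and selection rule.

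**Conclusion.** The concern holds in a limited form. The article fixes accuracy as primary, selects by an unweighted balance, and lists no calibration measure for a tool described as predicting risk. Over-extreme risks with unchanged ranking would go undetected: a slope of 0.5 and a Brier score of 0.218 rather than 0.205 leave every listed metric the same at a 0.5 cut. Severe overfitting would probably be caught by the planned checks; moderate miscalibration can pass them. The accuracy floor is about 59% at the assumed prevalence, and 50% to 70% if Tilburg prevalence is 50% to 70%.

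These sizes rest on the article's prevalence and R², a normal linear predictor, the 0.5 cut and, for the sample-size link, a shrinkage target of 0.9. The overfitting figures further assume unpenalised models without variable selection. The gap itself, with no listed metric measuring calibration, depends on none of these.

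**What to change.** The Results section says that no data have been analysed, so the following can still be prespecified:

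- Replace accuracy as primary with one selection rule based on a proper score, for example the lowest cross-validated Brier score or log-loss. Either is acceptable if named in advance.
- Report AUC, calibration intercept, calibration slope and a calibration plot, with 95% confidence intervals, in both internal and temporal validation.
- Keep accuracy, precision, recall and F1 as secondary, at a prespecified threshold, with the majority-class accuracy printed beside them.

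The cost is a little more analysis and some rewording. The headline figures will look less flattering.

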### Patient Recruitment

All eligible patients will be recruited within 24 to 48 hours after admission. Trained researchers will determine potential participants based on inclusion and exclusion criteria and explain this observational study to patients and their families. After patients confirm and sign informed consent forms, they will be included in this study. The examination results and related data of all participants will be subject to strict confidentiality management to ensure the privacy and security of patients. Participants have the right to withdraw from the study in any form at any stage. We plan to recruit at least 556 hospitalized older adults living with HIV or AIDS (n=445 for development and n=111 for validation). The research evaluation will be completed during the patient’s hospitalization period.

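### Predictor screening from 31 candidates appears to sit outside the cross-validation and bootstrap, so internal performance would be too high and the AUC-gap check could not see selection overfitting

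*Protocol article*

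**What the plan says.** - **Candidates.** Under Determination of Candidate Variables, "a total of 31 candidate predictor variables were identified".
- **Screening.** The abstract's Methods paragraph says: "Potential predictors are screened using univariate analysis and least absolute shrinkage and selection operator regression to identify variables for final model inclusion". Model Development and Validation says: "Univariate analysis combined with least absolute shrinkage and selection operator regression will be used to screen predictive factors". Each text names the step once. In the latter it follows the instruction "Randomly split the training set and validation set in a 7:3 ratio".
- **Cross-validation.** The same section says: "A 3×10-fold cross-validation scheme will be adopted, with each split performed independently, yielding 30 model performance estimates". It names what this covers: "To prevent overfitting, the nonlinear modeling effects of all models will be validated via cross-validation". It also names the parameters tuned there: tree depth for the random forest, and C and γ for the support vector machine. Variable screening and the LASSO penalty are not in that list.
- **Overfitting check.** The training and cross-validated AUC are to differ by less than 0.05.
- **Bootstrap.** In 1,000 resamples the models are retrained and re-evaluated. Repeating the screening is not mentioned.
- **Later assessment.** The chosen model goes to an independent test set, and a temporal cohort from September to December 2025 serves as external validation.
- **Choice of algorithm.** Accuracy is the primary metric, weighed against precision, recall, F1 and AUC.

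**The concern.** If predictors are picked once using all the training data, every held-out fold has already helped to pick them. Refitting coefficients fold by fold does not undo that. The held-out estimate is then optimistic, and cross-validation cannot see the overfitting that comes from choosing among 31 candidates.

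The AUC-gap rule is the plan's only numerical overfitting check. It compares two quantities that share the same leak, so the gap looks small whether or not selection has overfitted. A bootstrap that refits a fixed predictor list has the same blind spot. The study would report internal performance that is too good and a safeguard that passes almost automatically.

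**Working it through.** **1. The plan's own figure.** The article gives no figure for optimism. Its sample size supplies the signal strength, so I checked that first. With 10 parameters, Cox-Snell R² 0.1483 and target shrinkage 0.9 (the value that reproduces the plan's figure):

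n = 10 / [(0.9 − 1) × ln(1 − 0.1483/0.9)] = 555.4, rounded up to 556.

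Events: 556 × 0.593 = 329.7, or 33.0 per parameter. Both agree with Sample Size. They do not bear on the point except as inputs.

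**2. Inputs from the article.** 31 candidates; prevalence 0.593; R² 0.1483. Two development sizes were used because the article gives two: 0.7 × 556 = 389 from the 7:3 split, and 445 from Patient Recruitment ("n=445 for development and n=111 for validation").

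**3. Assumptions.** Independent normal predictors. Univariate screen at P < .05, a threshold the article states only for baseline comparisons. Then LASSO with a 5-fold cross-validated penalty and a logistic refit. The signal is spread equally over 5, 10 or all 31 predictors, or is absent. Logistic model only; 100 replicates per setting; one 10-fold run per replicate; true AUC from 5,000 new subjects.

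**4. Comparison.** Screening was either done once on all training data or repeated in each training fold. Optimism is the cross-validated AUC with one screen minus the true AUC, from unrounded means (standard error at most 0.004). The last two columns give the share of replicates in which training AUC minus cross-validated AUC was below 0.05. Training AUC is that of the model screened and fitted on the full training set.

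| n | Predictors with signal | Training AUC | CV AUC, screened once | CV AUC, screened in folds | True AUC | Optimism | Check passes, once | Check passes, in folds |
|---|---|---|---|---|---|---|---|---|
| 389 | none | 0.572 | 0.567 | 0.504 | 0.500 | 0.068 | 100% | 34% |
| 389 | 5 | 0.740 | 0.723 | 0.698 | 0.701 | 0.022 | 100% | 67% |
| 389 | 10 | 0.736 | 0.713 | 0.668 | 0.674 | 0.038 | 99% | 27% |
| 389 | 31 | 0.718 | 0.689 | 0.607 | 0.616 | 0.073 | 99% | 1% |
| 445 | none | 0.574 | 0.567 | 0.506 | 0.500 | 0.068 | 100% | 31% |
| 445 | 5 | 0.740 | 0.725 | 0.705 | 0.707 | 0.018 | 100% | 87% |
| 445 | 10 | 0.736 | 0.713 | 0.674 | 0.681 | 0.032 | 100% | 28% |
| 445 | 31 | 0.718 | 0.691 | 0.619 | 0.619 | 0.072 | 100% | 0% |

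Screening within folds comes within about 0.01 of the true AUC in every row.

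**5. The check against the truth.** Training AUC minus true AUC at n = 389 is 0.072, 0.039, 0.062 and 0.102 down the rows; at n = 445 it is 0.074, 0.033, 0.055 and 0.099. In three of the four signal settings at each size the real gap exceeds 0.05 on average, yet with one screen the check passes in 99 to 100% of replicates.

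**6. Accuracy.** Cross-validated accuracy with one screen exceeds true accuracy by 0.010 (0.675 − 0.665; n = 445, 5 predictors) to 0.046 (0.652 − 0.606; n = 389, 31 predictors).

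**7. Sensitivity to the signal.** A separate simulation at n = 389, with 40,000 new subjects for the truth, gave:
- at the plan's R²: 0.713 against a true 0.699, optimism 0.014;
- at about half that signal: 0.632 against 0.606, optimism 0.026;
- with no signal: 0.571 against 0.500, optimism 0.071.

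A third, with 5 or 10 true predictors, gave 0.021 to 0.039 at the plan's R², 0.013 to 0.014 at a true AUC near 0.80, and 0.006 to 0.007 near 0.85.

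**8. Bootstrap.** This was reasoned, not simulated. If every resample reuses one predictor list, the variation due to selection never enters the estimate.

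**The case against.** **The order is inferred.** A reader might take the article to state that screening is a one-off step outside the folds. It does not say that screening is repeated, nor that it is not. A condensed article may leave nesting to a fuller plan, and the flow chart is not shown. This stands as a limit on certainty. It does not dispose of the point: the article gives the fold scheme, the number of estimates, the tuned parameters and a numerical threshold, and an analyst who follows that text would screen once.

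**Imputation.** A reader might infer that multiple imputation comes before the split. Statistical Analysis mentions neither split nor folds, so the text does not support this.

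**Choice of model.** It would be too strong to say that an inflated AUC picks the final model. Accuracy is primary and the choice rests on a balance of metrics. The three algorithms appear to share one screened list, so much of the inflation may be common to them, and only logistic regression was simulated. A wrong choice of algorithm is not shown.

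**Later safeguards.** The test set and temporal cohort are real protection, and the split is named before the screening. Both are free of this bias if screening uses training data alone and the temporal cohort stays out of model building. They do not repair the cross-validation check or the bootstrap estimate.

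**Size.** Several candidates overlap the content of the Tilburg scale (nutrition with weight and mobility, mood, cognition, social support), so the signal may be stronger than assumed and the optimism smaller. This stands, and the no-signal rows should be read as a limiting case.

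**Conclusion.** The point holds on the natural reading of the text. With screening done once, cross-validated AUC and accuracy are too high, bootstrap performance shares the defect, and the 0.05 AUC-gap rule cannot detect overfitting from predictor selection. AUC optimism is about 0.01 to 0.07. It depends on the assumed signal and on how many predictors carry it, and falls to about 0.013 at a true AUC near 0.80 and below 0.01 near 0.85. Accuracy is overstated by about 0.01 to 0.05.

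These sizes rest on independent normal predictors, a P < .05 screen and a logistic model; correlated or categorical predictors would change them. The direction was the same in every setting run. The conclusion concerns the level of internal performance. It does not show that the algorithms would be ranked wrongly or that the final test-set result is biased. The latter depends on screening being confined to training data, which the article leaves unstated.

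**What to change.** State in Model Development and Validation that:

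1. univariate screening, LASSO with the choice of its penalty, spline choice and hyperparameter tuning use training data only;
2. all of these are rerun within each of the 30 cross-validation training folds, with tuning in an inner loop, and applied unchanged to the held-out fold;
3. the same sequence is rerun in each of the 1,000 bootstrap resamples;
4. the predictor list from the full training set is used only for the final fitted model, which is then assessed on the untouched test set and temporal cohort.

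If this is already intended, a sentence or two settles it. The same text could usefully say where multiple imputation sits relative to the split and folds.

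The cost is a pipeline script, more computing time and somewhat lower reported internal performance. No new data are needed, and the Results section says that no analysis has yet been done, so the change can still be made in advance.
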